### Primary Outcome Measures

#### Number of Whole-Body Bone Lesions on 18F-Choline PET/CT and 18-FDG PET/CT

Every bone lesion will be validated using the reference standard, which is WB-MRI. A bone lesion that is not present on MRI but is present on any of the PET modalities must be validated by an expert multidisciplinary consensus.

#### Number of Bone Lesions Within Defined Skeletal Areas on 18F-Choline PET/CT and 18-FDG PET/CT

The following 6 skeletal areas will be defined: skull, spine, pelvis, sternum and ribs, superior limbs, inferior limbs. The number of bone lesions in each of these skeletal areas is assessed. Each bone lesion must be validated as mentioned in the previous paragraph.

### Secondary Outcome Measures

#### Diagnostic Accuracy of 18F-Choline PET/CT and 18-FDG PET/CT for the Detection of Focal Bone Lesions

Sensitivity, specificity, positive and negative predictive values, and diagnostic likelihood ratios of each test will be calculated based on two different reference tests. The first reference test will be standard MRI sequences (T1-weighted turbo spin echo sequences, T2-STIR). The second reference test will be a reference standard composed of standard MRI sequences plus DW WB-MRI acquisitions.

#### Diagnostic Accuracy of 18F-Choline PET/CT and 18-FDG PET/CT for the Detection of Diffuse Infiltration of the Spine

Sensitivity, specificity, positive predictive value, negative predictive value, and diagnostic likelihood ratios of each test will be calculated based on WB-MRI results.

#### Number of Extramedullary Lesions on 18F-Choline PET/CT and 18-FDG PET/CT

The number of extramedullary lesions detected by each test will be compared.

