#### Interpretation Criteria

After anonymization, images will be independently read by two experienced nuclear medicine physicians, blinded from clinical data, biological data, and other imaging data performed during the protocol.

18F-choline has physiological uptake by the liver, spleen, pancreas, salivary glands, and urinary tract. Lymph node uptake will not necessarily be considered pathological, particularly in the mediastinum, as lymphadenitis and granulomatosis are sources of false positive findings. Any focal bone uptake will be considered pathological if the uptake is superior to that of surrounding background activity. The following 6 skeletal areas will be defined: skull, sternum-ribs, spine, pelvis, superior limbs, and inferior limbs. The number of focal lesions (FL), localization, and intensity of uptake (SUVmax) will be described for each skeletal area. Diffuse infiltration of the spine will be defined as diffuse spine uptake that is superior to liver uptake [11,14].

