#### Interpretation Criteria

After anonymization, images will be independently read by two experienced nuclear medicine physicians, blinded from clinical data, biological data, and other imaging data performed during the protocol.

18-FDG has physiological uptake by the brain, myocardium, kidneys, urinary tract, liver, and spleen. A focal bone lesion is defined as a focal uptake that is superior to surrounding background uptake. An extramedullary lesion will be considered if there is focal uptake within organ or lymph node structures. Of note, bilateral mediastinal lymph node uptake will not be considered as disease, as this will more likely correspond to granulomatosis lesions like sarcoidosis. The same 6 skeletal areas will also be used to classify focal bone lesions. The number of FL, localization, and SUVmax will be retrieved for each skeletal area. Diffuse infiltration will be defined as diffuse spine uptake that is superior to liver uptake [11,14].

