### Sample Size Calculation and Statistics

The main objective is to compare the number of FL detected on 18F-choline PET/CT and 18-FDG PET/CT, after confirming that each lesion exists on the reference standard. Data from a recent article showed that 18F-choline detects 75% more bone lesions than 18-FDG PET/CT [22]. Intrapatient concordance was 0.85. For each tracer, the standard error and mean of the distribution of the number of lesions wsere equal. We hypothesized that we will observe an average number of 10 bone lesions on 18-FDG PET/CT and that this number will increase by 75% on 18F-choline.

With a type I error of 5% and power of 90%, it will be necessary to include 23 patients. Due to the probability that the number of lesions will not follow a normal distribution, we will use a Wilcoxon signed-rank test, which is less powerful than the Student *t* test. To compensate for this lack of power, we will include 30 patients.

The secondary objectives are to compare the global accuracy of 18F-choline PET/CT and 18-FDG PET/CT as well as the accuracy of these two modalities in each of the 6 skeletal areas defined earlier for the detection of MM bone lesions. Accuracies of each modality will be compared using the McNemar test. Other secondary objectives will include the comparison of the accuracies of 18F-choline PET/CT and 18-FDG PET/CT for detecting diffuse infiltration of the spine using the McNemar test. Comparison of the number of extramedullary lesions detected by 18-FDG PET/CT and 18F-choline PET/CT will be performed using the Wilcoxon signed-rank test.

Interobserver and intraobserver agreements of PET/CT readings will be evaluated using the Cohen kappa coefficient.

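### Extramedullary lesions are compared as unconfirmed counts read under unequal rules for the two tracers, so a difference need not mean better detection of disease

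*Protocol article*

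**What the plan says.** Under Secondary Outcome Measures, the whole definition of this outcome is "The number of extramedullary lesions detected by each test will be compared". Sample Size Calculation and Statistics adds the test: "Comparison of the number of extramedullary lesions detected by 18-FDG PET/CT and 18F-choline PET/CT will be performed using the Wilcoxon signed-rank test".

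The positivity rules are in the two Interpretation Criteria sections.

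- **FDG:** "An extramedullary lesion will be considered if there is focal uptake within organ or lymph node structures", with one fixed exception: "bilateral mediastinal lymph node uptake will not be considered as disease".
- **Choline:** no extramedullary definition. The positivity rule that is given concerns bone: "Any focal bone uptake will be considered pathological if the uptake is superior to that of surrounding background activity". On nodes it says: "Lymph node uptake will not necessarily be considered pathological, particularly in the mediastinum, as lymphadenitis and granulomatosis are sources of false positive findings".

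For the primary outcome, by contrast, "Every bone lesion will be validated using the reference standard, which is WB-MRI", and a bone lesion seen on PET but not on MRI needs expert consensus. The Reference Standard section describes that consensus for each FL (focal lesion) absent from MRI. It draws on the patient's records, all three baseline scans and the response of the lesion over 12 months.

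**The concern.** In a comparison of raw counts a false-positive focus scores exactly like a true lesion. A tracer can lead because it finds more disease, because it lights up more benign nodes, or because its reading rule admits more foci. The article itself names lymphadenitis and granulomatosis as sources of false positives. The bone outcomes are protected by validation, and diffuse infiltration is judged against WB-MRI. The extramedullary outcome has neither safeguard, and its two counts do not come from the same rule. What is at stake is how this one secondary result may be read: the Wilcoxon p-value could not be taken as evidence that one tracer detects more extramedullary disease.

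**Working it through.** **The plan's own figure.** None is stated for the extramedullary comparison. The only calculation is for bone lesions: means 10 and 17.5, SD equal to the mean, concordance 0.85 used as the correlation. SD of the difference = √(10² + 17.5² − 2 × 0.85 × 10 × 17.5) = √108.75 = 10.43. With a difference of 7.5, a two-sided 5% paired t-test at 90% power gives n = 23 (power 0.909), as stated. It has no bearing on extramedullary counts.

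**The same focus under the two reading rules.**

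| Focus | FDG | Choline |
|---|---|---|
| Organ | Positive by rule | No rule stated |
| Non-mediastinal node | Positive by rule | Reader's decision |
| Unilateral mediastinal node | Positive by rule | Reader's decision |
| Bilateral mediastinal nodes | Negative by rule | Reader's decision |

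No row has the same rule in both columns. For nodes, FDG is looser in two rows of three and stricter in the third.

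**Does the consensus step cover these foci?** Both PET sections tally FL by skeletal area. The MRI section defines FL on DW images against the marrow background and gives no extramedullary criterion. Both primary-outcome paragraphs attach validation to bone lesions. The natural reading is that extramedullary foci are outside it.

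**Mechanism, with assumed rates.** Expected raw count per patient = (sensitivity × true lesions) + false positives. Assume 0.5 true lesions per patient and 80% sensitivity for both tracers. With 0.3 false positives per patient for tracer A and 0.1 for B:

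- A: 0.8 × 0.5 + 0.3 = 0.70
- B: 0.8 × 0.5 + 0.1 = 0.50

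The true-positive parts are identical, so the gap of 0.20 is all false positives. In general, a less sensitive tracer A leads on raw counts once its excess of false positives exceeds true lesions × (sensitivity of B − sensitivity of A). At 60% against 90% that is 0.5 × 0.3 = 0.15 per patient.

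Simulation under these assumptions (30 patients, overdispersed lesion numbers, two-sided 5% signed-rank test in its large-sample form, 3,000 trials per row):

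| Sensitivity A / B | False positives per patient A / B | A significantly ahead |
|---|---|---|
| 80% / 80% | 0.1 / 0.1 | 1.9% |
| 80% / 80% | 0.3 / 0.1 | 28% |
| 80% / 80% | 0.5 / 0.1 | 70% |
| 80% / 80% | 1.0 / 0.1 | 99.7% |
| 60% / 90% | 0.5 / 0.1 | 32% |
| 60% / 90% | 1.0 / 0.1 | 94% |
| 80% / 80%, true lesions only | none | 1.7% |

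Counting true lesions only, the test rejects in 2.9% of trials, both directions together. The three- to tenfold imbalance in false positives is an input. The table shows that the mechanism works, not how large it is in this trial.

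**The case against.** **The consensus may already apply.** The Methods paragraph of the Abstract and the Reference Standard section speak of focal lesions without the word bone, so a reader could include extramedullary foci. This stands as an ambiguity. It does not settle the matter, because FL is used elsewhere only for skeletal or marrow lesions and MRI has no criterion by which an extramedullary focus would be present or absent.

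**The aim is a detection rate, not accuracy.** The Objective does separate the two, and no sensitivity is claimed for this outcome. But a detection is of interest only if the thing detected is disease, and the bone detection count is validated for that reason.

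**The article is condensed, and both sections urge the same caution about nodes.** A full protocol may supply a choline definition. Still, the article prints a fixed rule for one tracer and a discretionary one for the other, and it ties validation to bone. The mismatch is between stated rules.

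**Stronger readings.** A reader might infer that a significant result would more likely reflect false nodal calls than disease. The route would be this: an exact two-sided signed-rank test has minimum p = 2 × 0.5^k for k patients with a non-zero difference, which is 0.0625 at k = 5 and 0.031 at k = 6. If 5%, 10% or 15% of patients truly differed (assumed), the chance of at least 6 in 30 is 0.3%, 7% or 29%. That shows little power for true differences. It says nothing about how often false calls occur, and the documents give no rate for either, so the inference fails. A reader might also infer a bias towards choline. Taken alone, the nodal wording leans towards FDG, and the remaining influences are unknown.

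**Conclusion.** The point holds for the design of this outcome. As written, extramedullary counts are compared without a stated confirmation step and under unequal positivity rules, so a difference cannot be attributed to detection of disease. This rests on reading FL as bone or marrow lesions, which is how the article uses the term.

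No size can be given for the bias. Any figure depends on assumed extramedullary and false-positive rates, and the net direction is open. The matter should be corrected, but it concerns one secondary outcome for which no sample size was calculated, and it leaves the primary comparison of validated bone lesions intact.

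**What to change.** 1. State one extramedullary definition for both tracers, with the same nodal exclusion, in both Interpretation Criteria sections.
2. State in the Reference Standard section that the multidisciplinary consensus also covers extramedullary foci, using the same evidence as for bone.
3. Base the Wilcoxon comparison on confirmed lesions, and report unconfirmed counts for each tracer beside them.

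The cost is revised reading wording and a few more cases for the existing panel, with no new scans. Enrolment was continuing, with 8 participants included as of June 2020; any scans already read would need their extramedullary item scored again under the shared rule. If MRI is to serve for confirmation, its Interpretation Criteria need an extramedullary criterion, which they now lack. Otherwise the panel can carry the confirmation.

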### Sample Size Calculation and Statistics

The main objective is to compare the number of FL detected on 18F-choline PET/CT and 18-FDG PET/CT, after confirming that each lesion exists on the reference standard. Data from a recent article showed that 18F-choline detects 75% more bone lesions than 18-FDG PET/CT [22]. Intrapatient concordance was 0.85. For each tracer, the standard error and mean of the distribution of the number of lesions wsere equal. We hypothesized that we will observe an average number of 10 bone lesions on 18-FDG PET/CT and that this number will increase by 75% on 18F-choline.

With a type I error of 5% and power of 90%, it will be necessary to include 23 patients. Due to the probability that the number of lesions will not follow a normal distribution, we will use a Wilcoxon signed-rank test, which is less powerful than the Student *t* test. To compensate for this lack of power, we will include 30 patients.

The secondary objectives are to compare the global accuracy of 18F-choline PET/CT and 18-FDG PET/CT as well as the accuracy of these two modalities in each of the 6 skeletal areas defined earlier for the detection of MM bone lesions. Accuracies of each modality will be compared using the McNemar test. Other secondary objectives will include the comparison of the accuracies of 18F-choline PET/CT and 18-FDG PET/CT for detecting diffuse infiltration of the spine using the McNemar test. Comparison of the number of extramedullary lesions detected by 18-FDG PET/CT and 18F-choline PET/CT will be performed using the Wilcoxon signed-rank test.

Interobserver and intraobserver agreements of PET/CT readings will be evaluated using the Cohen kappa coefficient.

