### Reference Standard

The reference standard is WB-MRI, which is comprised of conventional MRI sequences combined with WB-MRI diffusion acquisition. Each FL found on 18F-choline or 18-FDG PET/CT and not present on MRI will undergo multidisciplinary consensus between hematologists, nuclear medicine physicians, and radiology physicians. A decision will be reached and will classify an FL as a true-positive or false-positive finding based on patient charts and results from 18-FDG PET/CT, 18F-choline PET/CT, and WB-MRI at baseline but also based on lesion response to chemotherapy during a 12-month follow-up.

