## Discussion

### Overview

A recent study showed that the rate of false-negative results for 18-FDG PET/CT for the detection of bone disease in MM is about 10%, which could be attributed to a lower expression of hexokinase 2 [13]. A more sensitive tracer is therefore needed.

The role of 18F-choline in the management of relapsed prostate cancer is well-established, and it also has a role in the characterization of hepatocellular carcinoma. However, it remains poorly explored in the field of hematological diseases. 18F-choline is incorporated into the membrane of cells in division and could reflect the higher rate of neoplastic plasma cells.

A recent retrospective study has shown that 18F-choline detects 75% more focal bone uptakes than 18-FDG PET/CT [18]. However, this study was performed on a heterogeneous previously treated population with suspected progressive disease or relapse. It is known that 18-FDG metabolism in myeloma cells can change after first-line treatment and that FDG-negative myeloma cases at diagnosis can turn FDG-positive when they relapse [13].

This prospective comparative study of diagnostic accuracies will evaluate if 18F-choline PET/CT is superior to 18-FDG PET/CT in a homogenous population with de novo MM. The expected role (according to STARD 2015 definitions) of 18F-choline PET/CT is the replacement of 18-FDG PET/CT. The study has been designed to comply with QUADAS 2 guidelines. We will carefully exclude patients that are already being treated with corticosteroids because of the increased risk of false-negative findings on 18-FDG PET/CT and patients that had a recent injection of bone marrow stimulation factors because of the risk of a false-positive assessment of bone marrow on PET/CT and MRI [14]. Also, 18-FDG PET/CT, 18F-choline, and WB-MRI will be performed within a short time period to avoid misinterpretation due to the apparition of new bone lesions during the protocol.

By analyzing the number of bone lesions per skeletal area, we expect to find that 18F-choline is superior to 18-FDG PET/CT for the detection of bone lesions, especially in the skull, as 18F-choline has no brain uptake. A previous study showed that the median uptake of 18F-choline is higher than that of 18-FDG [18]. Hence, we expect that 18F-choline PET/CT will be more sensitive than 18-FDG PET/CT for the detection of focal bone lesions as well as for the detection of diffuse infiltration.

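### The global focal-lesion accuracy comparison has no fixed unit: counted by lesion, specificity cannot be computed and the ordinary McNemar test ignores clustering by patient

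*Protocol article*

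**What the plan says.** Under Sample Size Calculation and Statistics, a secondary aim concerns the detection of myeloma bone lesions, both globally and by region. It reads (cut here before its noun, areas): "compare the global accuracy of 18F-choline PET/CT and 18-FDG PET/CT as well as the accuracy of these two modalities in each of the 6 skeletal". The method is one sentence: "Accuracies of each modality will be compared using the McNemar test". The same test is named for a further objective, the "comparison of the accuracies of 18F-choline PET/CT and 18-FDG PET/CT for detecting diffuse infiltration of the spine using the McNemar test".

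The matching outcome under Secondary Outcome Measures is headed "Diagnostic Accuracy of 18F-Choline PET/CT and 18-FDG PET/CT for the Detection of Focal Bone Lesions". It states: "Sensitivity, specificity, positive and negative predictive values, and diagnostic likelihood ratios of each test will be calculated based on two different reference tests".

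The section Reference Standard covers lesions seen on either PET but not on MRI: a consensus decision "will classify an FL as a true-positive or false-positive finding". The reading rules for choline PET add: "The number of focal lesions (FL), localization, and intensity of uptake (SUVmax) will be described for each skeletal area". The FDG rules record the same items. No section says what counts as a true negative for focal lesions, or names the unit of the two-by-two table.

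**The concern.** A patient may have many lesions and always has six areas. McNemar's test compares the two kinds of discordant pair on the assumption that pairs are independent. If one patient supplies many pairs that tend to favour the same tracer, the difference varies more than the test allows for and its p-value is too small.

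The protocol gives a reason to expect this. The Discussion (Overview) puts FDG false negatives at about 10%, "which could be attributed to a lower expression of hexokinase 2". If that is a property of the patient's tumour, it would affect many of that patient's lesions together.

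The second difficulty is the denominator. Lesion-free bone does not come in countable units, so a lesion-level table has no true-negative cell. Specificity, negative predictive value and both likelihood ratios then cannot be computed, and overall accuracy cannot either.

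At stake is the secondary accuracy evidence for the role the Discussion gives to choline PET, namely replacing FDG PET. The global comparison could show a tracer difference that is not there, or could rest on an arbitrary number of negatives.

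**Working it through.** **Inputs from Sample Size Calculation and Statistics.** Mean 10 lesions on FDG and 10 × 1.75 = 17.5 on choline; standard error equal to the mean, read as SD (10 and 17.5); intrapatient concordance 0.85, read as a correlation; 5% type I error; 90% power; 30 patients enrolled.

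**Step 1: reproduce the protocol's own figure.** SD of the paired difference = √(10² + 17.5² − 2 × 0.85 × 10 × 17.5) = √108.75 = 10.43. With a difference of 7.5, a two-sided paired t-test at 5% needs 23 patients (power 90.9%). This matches the stated 23 and supports the two readings above. One-sided, it would be 18.

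**Step 2: lesions as pairs, no true difference.** Let b and c be confirmed lesions seen only by choline and only by FDG. Within a patient, b − c equals D, the difference in lesion counts. The ordinary McNemar test takes the variance of b − c as E(b + c); with patients as clusters it is Var(D).
- Equal means of 10, SD 10: Var(D) = 2 × 10² × (1 − 0.85) = 30 per patient.
- E(b + c) cannot exceed 10 + 10 = 20 per patient, and reaches 20 only if no lesion is seen by both tracers.
- Design effect = Var(D) / E(b + c). Actual type I error = 2 × [1 − Φ(1.96 / √design effect)].

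| Discordant lesions per patient | Share of maximum | Design effect | Actual type I error |
|---|---|---|---|
| 20 | 100% (bound) | 1.5 | 11% |
| 10 | 50% (assumed) | 3.0 | 26% |
| 6 | 30% (assumed) | 5.0 | 38% |
| 4 | 20% (assumed) | 7.5 | 47% |

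With both means at 13.75, midway between 10 and 17.5, Var(D) = 56.7 and the maximum is 27.5. The design effect is then at least 2.06 and the error at least 17%.

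**Step 3: lesions as pairs, planned effect.** Discordance lies between 7.5 and 27.5 per patient. Ordinary z = 30 × 7.5 / √(30 × discordance), which is 15 down to 7.8. Clustered on patient, z = 30 × 7.5 / √(30 × 108.75) = 3.9 (p = 8 × 10⁻⁵). The evidence is overstated, but the conclusion would not reverse.

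**Step 4: other units, no true difference.** Simulation of 30 patients, 20,000 runs, with 20% or 40% of pairs discordant and an intracluster correlation of 0 to 0.5 in the direction of discordance. All of these settings are assumed.

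| Unit and test | Actual type I error |
|---|---|
| Six areas pooled (180 pairs), ordinary McNemar, 20% discordant | 5.1% (correlation 0) to 10.9% (0.5) |
| Same, 40% discordant | 5.1% to 16.4% |
| 180 pairs, test clustered on patient | 4.8% to 5.3% |
| One pair per patient, ordinary McNemar | 4.2% to 4.9% |

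**The case against.** The article never says that lesions or areas are pooled as independent pairs. Several readings keep one pair per patient: a single area scored once per patient, global accuracy scored per patient, and diffuse spine infiltration. McNemar is valid for all of these. The six areas also supply natural negatives, so planning specificity fits an area or patient unit at least as well as a lesion unit. The true/false-positive wording is an adjudication rule for PET lesions absent on MRI, not a definition of the analysis unit. A full protocol or analysis plan may settle all this. The outcomes are secondary, and the primary Wilcoxon test uses one pair of counts per patient.

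Most of this stands and sets the limits of the point. A reader might infer that every McNemar test here is invalid, or that true negatives do not exist at all. The documents support neither: single-area and diffuse-spine tests can have one pair per patient, and an area or patient with no lesion on the reference is a proper negative. A reader might also turn the 10% FDG false-negative rate into a share of wholly non-avid patients for both tracers and obtain a much larger error, such as 50% by lesion and 18% by pooled area with detection probability 0.8. The documents give no such rate for choline and no such detection probability.

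The objection does not remove the conflict in what is written. The article goes beyond silence: it names a test and a list of measures, heads the outcome as focal lesions and adjudicates lesion by lesion. A lesion-level reading is plausible, and under it the listed measures cannot be produced. Pooling lesions or areas would also require replacing the named test.

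**Conclusion.** The point holds for the global focal-lesion comparison only, and conditionally on the unit.
- **Lesions as units:** specificity, negative predictive value and likelihood ratios cannot be computed. An ordinary McNemar test has a type I error of at least 11%. The 26% to 47% range needs the assumed discordance shares.
- **Areas pooled:** inflation is none to moderate, about 5% to 16%, governed by a correlation the protocol does not give.
- **One pair per patient:** no problem.

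The 11% bound rests on reading the stated standard error as SD and the concordance as a correlation, on equal means of 10 for the null case, and on the planning inputs applying to confirmed lesions. Because this is a secondary analysis and the primary test is untouched, it should be fixed but is not critical to the trial.

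**What to change.** - Define the unit of the global focal-lesion comparison as patient by skeletal area, scored as lesion present or absent on the reference standard. With all six areas this gives 30 × 6 = 180 pairs and true negatives that can be counted.
- Compare sensitivity in reference-positive areas and specificity in reference-negative areas separately, so that a gain in one cannot be offset by a loss in the other. Use a patient-clustered McNemar test (Obuchowski or Durkalski), GEE with patient as cluster, or a patient-level bootstrap.
- At lesion level, report only sensitivity and positive predictive value, with patient-clustered intervals.
- Keep the ordinary McNemar test where each patient contributes one pair: a single area, the whole patient, or diffuse spine infiltration.

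The cost is wording and programming; no new patients or images are needed, and area scores follow from the lesion counts already recorded per area. The downside is wider intervals and larger p-values for the global secondary comparison.

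### Cohen kappa is the only reader-agreement measure named, although the main PET reading is a lesion count and SUVmax is continuous

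*Protocol article*

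**What the plan says.** The last sentence of Sample Size Calculation and Statistics fixes the method for reader agreement: "Interobserver and intraobserver agreements of PET/CT readings will be evaluated using the Cohen kappa coefficient". It does not state the variable rated, the level (lesion, area or patient) or any weighting.

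The two Interpretation Criteria sections for PET say what the readings are. For each tracer, "images will be independently read by two experienced nuclear medicine physicians". For 18F-choline, "The number of focal lesions (FL), localization, and intensity of uptake (SUVmax) will be described for each skeletal area"; for FDG, "The number of FL, localization, and SUVmax will be retrieved for each skeletal area". Each reader also makes one categorical call on the spine, which for FDG reads: "Diffuse infiltration will be defined as diffuse spine uptake that is superior to liver uptake".

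The count carries the trial. The first primary outcome is "Number of Whole-Body Bone Lesions on 18F-Choline PET/CT and 18-FDG PET/CT", the second is the same count by skeletal area, and the statistics section opens with "The main objective is to compare the number of FL detected on 18F-choline PET/CT and 18-FDG PET/CT".

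**The concern.** Cohen kappa in its ordinary form is a measure for nominal categories. It credits exact matches only, so 10 lesions against 11 is penalised as heavily as 10 against 40. SUVmax is continuous and has no natural categories at all. The one named coefficient therefore suits part of what the readers record, but not the part on which the primary comparison rests.

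There are two ways to follow the sentence, and both leave a problem. Applied unweighted to counts, kappa can make readers who agree closely look poorly reproducible. Confined to yes/no calls, it leaves the reproducibility of the count unreported. What is at stake is how the reliability of the two PET readings is described, not the tracer comparison itself.

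**Working it through.** **Inputs from the article.** The assumed mean FDG count is 10 ("We hypothesized that we will observe an average number of 10 bone lesions on 18-FDG PET/CT"). A 75% increase gives 10 × 1.75 = 17.5 for 18F-choline. The spread is stated as equal to the mean, the within-patient concordance is 0.85, and 30 patients are planned.

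**Does the spread reproduce the plan's own figure?** The article calls the spread a standard error. Reading it as a standard deviation:

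- SD of the paired difference = √(10² + 17.5² − 2 × 0.85 × 10 × 17.5) = √108.75 = 10.43
- Difference = 17.5 − 10 = 7.5
- Paired t-test, two-sided 5%, 90% power: n = 23 (power 0.909)

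This matches the stated 23, so SD = mean is the right spread for what follows. The article gives no figure for reader agreement.

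**Assumptions.** The article gives no reader-error rate, so a range is used. True counts for 30 patients are drawn from a negative binomial with SD = mean, and two readers each miss lesions independently (3,000 runs per setting).

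**Formulas.**

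- Unweighted kappa = (p_o − p_e)/(1 − p_e), where p_o is the share of patients with identical counts and p_e the share expected by chance.
- Under this error model, with detection probability p, mean μ and SD σ, ICC ≈ p²σ²/(p²σ² + μp(1 − p)).

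| Missed per reader | Mean | p_o | Unweighted kappa | Linear-weighted kappa | ICC |
|---|---|---|---|---|---|
| 1% | 10 | 0.843 | 0.83 | 0.98 | 0.999 |
| 1% | 17.5 | 0.765 | 0.75 | 0.98 | 0.999 |
| 5% | 10 | 0.577 | 0.55 | 0.94 | 0.994 |
| 5% | 17.5 | 0.476 | 0.45 | 0.95 | 0.996 |
| 10% | 10 | 0.456 | 0.42 | 0.90 | 0.987 |
| 10% | 17.5 | 0.364 | 0.34 | 0.92 | 0.992 |

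Check on the ICC at 5% and mean 10: 0.9025 × 100 / (90.25 + 10 × 0.95 × 0.05) = 90.25/90.725 = 0.995, against 0.994 simulated.

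**Why kappa falls.** Counts spread over many values, so chance agreement is small. At 5% and mean 10 it is about (0.577 − 0.548)/(1 − 0.548) = 0.06. Unweighted kappa is then little more than the share of identical counts, and the size of a disagreement does not enter.

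**Size of the disagreement in lesions.** The variance of the difference between readers is 2μp(1 − p). At 5% missed this is 2 × 10 × 0.0475 = 0.95 for mean 10, so the 95% limits are ±1.96 × √0.95 = ±1.9 lesions. For mean 17.5 it is 1.6625, giving ±2.5 lesions. A kappa of 0.55 or 0.45 hides that.

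**Other error models.**

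- Readers differ by one lesion in 25%, 50% or all patients: unweighted kappa is about 0.74, 0.49 or 0 at both means, ICC at least 0.994, and linear-weighted kappa at least 0.90.
- Each reader misses 5% and adds 0.3 spurious foci per patient: unweighted kappa 0.37 (mean 10) and 0.32 (mean 17.5), ICC 0.990 and 0.995.

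**Would a yes/no call stand in for the count?** For the negative binomial with mean 10 and SD 10, the size is 100/(100 − 10) = 1.111 and P(0) = (1.111/11.111)^1.111 ≈ 0.08, or 2 to 3 of 30 patients. Patient-level presence or absence therefore says little about count reproducibility.

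**The case against.** The strongest reply is that the article never says kappa is unweighted or applied to raw counts. The readings include calls for which kappa is right: diffuse infiltration, and an area being positive or negative. Weighted kappa stays at about 0.90 or above in every setting tried, and a full protocol or analysis plan may set the variable and weights. This stands, and it makes the point conditional. It does not remove it, because the article names one coefficient for all PET readings and, on either way of following it, the count is poorly served or not served.

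Several stronger readings are tempting but not supported:

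- **That near-perfect readers would necessarily look poor.** With 1% of lesions missed, even unweighted kappa is 0.83 or 0.75.
- **That kappa is biased against 18F-choline.** At the same share of one-lesion differences, kappa is the same at means 10 and 17.5 (0.74 and 0.74; 0.49 and 0.49). It is lower for 18F-choline only when errors scale with the number of lesions, and the article plans no comparison of reader agreement between tracers.
- **That kappa fails because joint negatives do not exist.** An area that both readers call clear is a joint negative, and so is an MRI lesion that neither reader reports.
- **That the intraobserver analysis is contradicted and should go.** The Interpretation Criteria do not say that each physician reads only once. A re-reading schedule is a detail that an article may leave out.
- **That the primary endpoint is compromised.** Its lesions are validated by MRI or expert consensus, and reader agreement is not a listed outcome.

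**Conclusion.** The point holds in conditional form. The single agreement measure named does not suit the lesion count or SUVmax. If it is used unweighted on counts, reproducibility can be badly understated: about 0.83/0.75, 0.55/0.45 or 0.42/0.34 at 1%, 5% or 10% of lesions missed, against an ICC of at least 0.987. These values rest on the article's own mean and spread, but on reader-error rates that are assumed. The high ICC also partly reflects the wide spread between patients, which is why limits of agreement in lesions should go with it. The matter is confined to a supportive reliability analysis; the Wilcoxon test and the 23 and 30 patients are untouched.

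**What to change.** Replace the kappa sentence with one that matches the measure to the reading:

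- **Categorical readings** (area positive or negative, diffuse infiltration): Cohen kappa.
- **Lesion counts and SUVmax:** two-way absolute-agreement ICC with 95% CI, and Bland-Altman limits of agreement. Put counts on a square-root or log scale, adding one before the log because some counts will be zero.

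Keep the intraobserver analysis and apply the same split to it.

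The interobserver part needs no new data, since the two readers already record counts and SUVmax. The cost is a change of wording and a few lines of analysis.
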